## 2.2. Objectives

The aim of this study is to evaluate the safety and immunogenicity of the COVID-19 vaccine in the elderly aged 60–80 years.

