## 3.6. Sample size

The target sample size is 300 participants. The allocation ratio will be 2:1, with 200 participants in the elderly experimental group (aged 60–80) and 100 participants in the younger control group (aged 18–59).

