### 3.10.2. Statistical methods

**Principles of statistical analysis:**

All statistical analyses were performed using IBM SPSS (version 26).

Demographic analysis will be performed in FAS population, the primary analysis (safety) will be performed in the SS population, and the secondary analysis (immunogenicity) will be performed both in the FAS and PPS population.

The Kolmogorov-Smirnov test was used to evaluate the distribution types. Non-normally distributed and ordered data are represented by the median (range). Measurement of pseudovirus 50% neutralization titers (pVNT_50_s) are represented by geometric means. Pearson’s chi-square test, continuity correction, and Fisher’s exact test were used to check the proportion of the count data.

The Mann-Whitney U test and paired t-test were used to compare differences between groups, the Wilcoxon rank-sum test was used to compare intragroup differences, and the nest t-test was used to compare unmatched groups. We displayed the median values of each group in the figures using GraphPad Prism 8 and estimated the differences based on the 95% confidence interval (CI).

Baseline characteristics were screened using univariate logistic regression, and the significantly different factors (*P*_value<0.1) were further analyzed using multivariate logistic regression. The analysis results are presented using an OR combined with a 95% CI (lower–upper) in the table.

In correlation analysis, the Pearson correlation test was used to process normally distributed datasets, while the Spearman rank correlation test was used to process non-normally distributed datasets. An absolute R value>0.5 indicated a strong correlation, whereas an absolute R value≤0.5 indicated a weak correlation.

The hypothesis test was bilateral, and a *P*_value<0.05 was considered statistically significant.

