**Primary analysis:**

The main endpoint of this study is the safety after vaccination, which involves the evaluation of AEs, SAEs, and laboratory test indices, and performed on the SS.

The AEs/SAEs occurring in the two groups within one month after each dose of vaccination will be statistically described as a categorical variable, and Pearson’s chi-square test or Fisher’s exact test will be used for intergroup comparisons. The AEs/SAEs of the different categories will be summarized in percentages. The laboratory test indices at each follow-up point will be statistically described as continuous variables, and the Mann–Whitney U test will be used for intergroup comparisons. The median values of the laboratory test indices for the two groups will be calculated at each follow-up point, as well as the corresponding intergroup differences and 95% CIs.

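### For adverse events, the first primary component, the protocol fixes a between-group test and percentages but no interval, so a non-significant result could be misread as equal safety.

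*Protocol*

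**What the plan says.** Protocol section 3.4.1 lists AE incidence first among the primary safety measures, assessed within a month of each dose. Section 3.10.2, Primary analysis, names a chi-square or Fisher comparison on the Safety Set: "exact test will be used for intergroup comparisons. The AEs/SAEs of the different categories will be summarized in percentages". No confidence interval is named for an AE proportion or for the difference between groups.

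The same paragraph treats the laboratory indices differently: "The median values of the laboratory test indices for the two groups will be calculated at each follow-up point, as well as the corresponding intergroup". That sentence ends by promising the between-group difference with its 95% interval.

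Two other sentences in section 3.10.2 (Principles of statistical analysis) mention intervals, and neither covers AE proportions:
- One concerns medians in figures: "We displayed the median values of each group in the figures using GraphPad Prism 8 and estimated the differences based on the 95% confidence interval".
- The other follows the logistic screening of baseline characteristics, for which no outcome is named: "The analysis results are presented using an OR combined with a 95% CI (lower–upper) in the table".

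The only general criterion is two-sided: a P "value<0.05 was considered statistically significant". Section 3.6 gives the size, "200 participants in the elderly experimental group (aged 60–80) and 100 participants in the younger control group", without an assumed AE rate, effect size or power. Section 2.2 states the aim as to "evaluate the safety and immunogenicity of the COVID-19 vaccine in the elderly aged 60–80 years". No margin, acceptable rate or upper bound for AEs or SAEs appears anywhere.

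**The concern.** Evaluating safety in the elderly is mainly an estimation question: how frequent are AEs and SAEs, and how large an excess over the young group remains possible? A difference test asks only whether equality can be rejected. When it does not reject, the P value cannot separate a small true difference from a sample too small to show a large one.

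At 200 against 100 the second explanation is often plausible, and it is strongest for rare severe or serious events. If the AE result is reported as specified, a non-significant P value beside two percentages could be taken as reassurance that the data do not give. The protocol already specifies the interval that would prevent this for the laboratory part of the same endpoint.

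**Working it through.** **Inputs.** From the protocol: n = 200 elderly and 100 young (section 3.6), two-sided α = 0.05, Pearson chi-square or Fisher exact test (section 3.10.2). Assumed: the young-group AE rate, which the protocol does not give and which is therefore varied, and all 300 participants in the Safety Set. The protocol has no power figure to reproduce.

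**Miss rate, normal approximation.** With pooled rate p̄ = (100·p_Y + 200·p_E)/300:
- SE₀ = √[p̄(1−p̄)(1/100 + 1/200)]
- SE₁ = √[p_Y(1−p_Y)/100 + p_E(1−p_E)/200]
- power ≈ Φ[(|p_E − p_Y| − 1.96·SE₀)/SE₁]

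For 20% elderly against 10% young: p̄ = 50/300 = 0.1667, SE₀ = 0.0456, SE₁ = 0.0412. Power = Φ[(0.100 − 0.0895)/0.0412] = Φ(0.256) = 60%, so the miss rate is 40%.

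**Miss rate, exact.** The binomial probabilities are summed over all tables in which the test does not reject. For a true 10-point elderly excess:

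| Young | Elderly | Normal approx. | Chi-square | Fisher | Continuity-corrected |
|---|---|---|---|---|---|
| 2% | 12% | 11% | 9% | 10% | 14% |
| 5% | 15% | 25% | 23% | 25% | 30% |
| 10% | 20% | 40% | 39% | 41% | 46% |
| 15% | 25% | 49% | 48% | 50% | 55% |
| 20% | 30% | 55% | 54% | 57% | 60% |
| 30% | 40% | 61% | 60% | 62% | 65% |
| 40% | 50% | 63% | 62% | 64% | 67% |

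For smaller differences, chi-square (Fisher): 10% elderly against 5% young, 71% (73%); 5% against 1%, 59% (67%); 3% against 1%, 90% (94%).

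The excess detectable with 80% power is about 10.7, 12.9, 15.5, 16.7 and 17.1 points at young rates of 5, 10, 20, 30 and 40%.

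**What an interval would show.** Take identical observed rates of 20%, that is 40/200 and 20/100. The Wilson 95% limits are 15.0% to 26.1% (elderly) and 13.3% to 28.9% (young). The Newcombe limits for elderly minus young are:
- lower: −√[(0.2000 − 0.1505)² + (0.2888 − 0.2000)²] = −10.2 points
- upper: +√[(0.2609 − 0.2000)² + (0.2000 − 0.1334)²] = +9.0 points

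The simple Wald half-width with equal observed rates p is 1.96·√[p(1−p)(1/100 + 1/200)]: 7.2 points at 10%, 9.6 at 20%, 11.0 at 30% and 11.8 at 40%. With equal observed rates, a 10-point excess can be excluded only if the common rate is not far above 20%.

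**Zero events.** With no SAE in 200 elderly participants, the one-sided 95% upper bound is 1 − 0.05^(1/200) = 1.5%. The two-sided 95% upper limit is 1 − 0.025^(1/200) = 1.8%.

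**The case against.** The specified analysis is valid and conventional, and nothing in the paragraph is stated wrongly. Interval methods are often left to a statistical analysis plan, which is not at hand. With no equivalence or non-inferiority objective, the absence of a margin is not in itself an error. The pattern also looks systematic: in the Secondary analysis part of section 3.10.2, antibody-positive rates likewise get a test without an interval, while titers get one. Counts and percentages would let a reader compute the intervals. The miss rates come from the sample size, and reporting an interval does not change them.

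Most of this stands, and it makes the point one of reporting and interpretation. It does not remove it: the protocol names the test and the summary for AEs, and in the same paragraph specifies interval estimates for the other primary measures.

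Four stronger readings are tempting and not supported:
- A reader might infer that a non-significant result will be declared equal safety. The protocol attaches no conclusion to P ≥ 0.05 and makes no equivalence claim; the misreading is only possible.
- A reader might infer that a real excess would usually be missed. At assumed young rates of 10% and 15%, the chi-square test misses a 10-point excess 39% and 48% of the time, so it detects it more often than not.
- A reader might infer that the trial sets out to find an elderly excess. Section 2.2 gives no such direction.
- A reader might infer that the laboratory comparisons are much better powered, because a 0.5-SD shift would be detected about 98% of the time. That compares unequal effects. A 10-point AE excess is about 0.23–0.28 on the arcsine scale for young rates of 10–20%. Simulated Mann-Whitney miss rates for shifts of that size are 37%, 48% and 55%, close to the AE figures.

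**Conclusion.** The point holds as a weakness in how the protocol fixes the primary AE analysis: a between-group test and percentages, with no interval, for a question that is mainly one of estimation. A non-significant test at 200 against 100 is weak evidence on safety.

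Its size depends on an AE rate that the protocol does not give. For a true 10-point excess, the miss rate is about 40–60% if the young rate is 10–30%, about 23–25% at 5%, 9–10% at 2%, and slightly above 60% at 40%. For 3% against 1% it is about 90%. These figures assume the full 300 in the Safety Set; losses would make them worse. The missing interval is a fact of the text whatever the rate.

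**What to change.** In section 3.10.2, Primary analysis, for AEs and SAEs:
1. For each dose and for any dose, report each group's proportion with an exact (Clopper-Pearson) 95% interval, and the elderly-minus-young risk difference with a Newcombe 95% interval.
2. For SAEs and grade 3 events, also report the one-sided 95% upper bound in the elderly (1.5% if 0/200).
3. Base the safety conclusion on these intervals, naming the excess that the data do and do not exclude.
4. State that P ≥ 0.05 is not evidence of equal safety.

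The chi-square or Fisher test can stay beside these estimates. The change needs no further participants, visits or data. It costs some wording, a few more table columns, and a safety statement less favourable than one of no significant difference. It does not raise power.

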## 2.3. Trial design

This trial is investigator-initiated and adheres to the principles of good clinical practice. It is a multi-center, prospective, single-arm clinical study. The trial will include two participant groups: an elderly group aged 60 to 80 years and a younger control group aged 18 to 59 years.

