### 3.3.2. Intervention assignment

Both the experimental and control groups will receive two doses of the inactivated COVID-19 vaccine, administered on day 0 (baseline) and day 25±3. A third booster dose will be given 6 months after the second dose.

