## 3.4. Outcomes

### 3.4.1 Primary endpoint measures

- Safety profiles within one month after each vaccination dose, including:

1. The incidence of adverse events;
2. Liver function;
3. Kidney function;
4. Blood glucose;
5. Blood lipids;

- The definition and grade of AEs were evaluated according to the Common Terminology Criteria for Adverse Events, version 5.0:

1. Grade 1 (mild) - asymptomatic or mild symptoms, clinical or diagnostic observations only, intervention not indicated;
2. Grade 2 (moderate) - minimal, local, or non-invasive intervention indicated, limiting age-appropriate instrumental activities of daily living (ADL);
3. Grade 3 (severe or medically significant but not immediately life-threatening) - indication for hospitalization or prolongation of hospitalization, disabling and limiting self-care ADL.

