## 3.8. Allocation and vaccine management

### 3.8.1. Allocation

The participants will be assigned to either the experimental or control group in a 2:1 ratio based on age.

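### The primary laboratory safety analysis compares elderly with young at each visit without using the baseline values collected, so it picks up existing age differences and cannot detect a change common to both groups

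*Protocol*

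**What the plan says.** Section 3.4.1 defines the primary endpoint as "Safety profiles within one month after each vaccination dose, including" adverse events, liver function, kidney function, blood glucose and blood lipids. Four of the five items are laboratory measures.

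Section 3.10.2 (Primary analysis) fixes how the laboratory items are analysed in the Safety Set: "The laboratory test indices at each follow-up point will be statistically described as continuous variables". On how elderly and young are then tested against each other, it specifies that "the Mann–Whitney U test will be used for intergroup comparisons". It adds: "The median values of the laboratory test indices for the two groups will be calculated at each follow-up point", with intergroup differences and 95% CIs. It assigns these data no change from baseline, baseline adjustment or within-group comparison.

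On the groups, section 3.8.1 says: "The participants will be assigned to either the experimental or control group in a 2:1 ratio based on age". Section 3.3.2 says: "Both the experimental and control groups will receive two doses of the inactivated COVID-19 vaccine", and both then have the same booster. Section 2.3 describes the design this way: "It is a multi-center, prospective, single-arm clinical study", while also naming a younger control group.

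The schedule in section 3.5 marks the laboratory tests at screening and at V2 to V9. The only stated use of the baseline values is in the Demographic analysis, which compares the two groups at baseline in the Full Analysis Set.

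**The concern.** The objective in section 2.2 is safety and immunogenicity in people aged 60–80. For laboratory values, the natural question is whether they move after vaccination in that group. The planned contrast asks whether older and younger people differ at a visit. Because age defines the groups and exposure is the same, the elderly-minus-young difference is not a vaccine contrast.

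Two errors follow. A significant result may only reflect how the groups differed before the first dose. A non-significant result says nothing about a rise or fall that occurred in both. Either could be reported as a finding on the primary safety endpoint.

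**Working it through.** **Inputs from the protocol.** 200 elderly and 100 young (3.6; 200 + 100 = 300, ratio 2:1, as stated); two-sided 0.05 (3.10.2); Mann–Whitney U on the value at each visit. The protocol gives no SD, age difference, correlation or expected shift. Those below are assumptions, in SD units, with normal data.

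**Structure (no assumed figure needed).** Let the young have pre-vaccination level a and the elderly a + d. Let c be a shift after vaccination common to both, and e an extra shift in the elderly only.

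- Planned contrast at a visit: (a + d + c + e) − (a + c) = d + e. The common shift c has gone, and d is mixed with e.
- Change from baseline: elderly c + e, young c, difference e. The age difference d has gone, and c is visible within each group.

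Adding the same amount to every value leaves the ranks unchanged, so the Mann–Whitney result does not move with c.

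**False signals from age alone (c = e = 0).** Approximate power = Φ(d × √[(3/π) × n₁n₂/(n₁+n₂)] − 1.96). Here n₁n₂/(n₁+n₂) = 200 × 100/300 = 66.7, and √(0.955 × 66.7) = 7.98.

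| Assumed d (SD) | 7.98 × d − 1.96 | Rejection per visit, planned test |
|---|---|---|
| 0.2 | −0.36 | 36% |
| 0.3 | 0.43 | 67% |
| 0.5 | 2.03 | 98% |

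Simulation (2,000 trials per scenario, baseline-to-follow-up correlation 0.5 or 0.7) gives 67–68% at 0.3 SD and 97–98% at 0.5 SD. Mann–Whitney on change from baseline rejects about 5% throughout.

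**Blindness to a common shift.** With d = 0 and c = 0.3 or 0.5 SD, the planned test rejects 5.0–5.5% in simulation, which is its nominal level. With d = 0.5 SD it rejects about 97–98% whether c is 0, 0.3 or 0.5 SD, so the result carries no information on c.

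For a paired test, the SD of change is √[2(1 − r)]: 1.00 at r = 0.5 and 0.77 at r = 0.7. Signed-rank power for c = 0.3 SD is about Φ(0.3/SD × √[(3/π)n] − 1.96):

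- Elderly, n = 200, r = 0.5: 0.3 × 13.82 − 1.96 = 2.19, so 98.6% (simulation 98.6%). At r = 0.7 it is nearly 100%.
- Young, n = 100, r = 0.5: 0.3 × 9.77 − 1.96 = 0.97, so 83% (simulation 83%). At r = 0.7 the simulation gives 96%.

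**Masking.** If the elderly alone shift by −0.3 SD and this offsets an age difference of +0.3 SD, the planned test rejects 4.8% of the time. The same test on change rejects 65% (r = 0.5).

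**Visits against endpoint.** Doses are given at V1, V2 and V5. The visits about one month after a dose are V2, V3 and V6; the analysis runs at all eight post-baseline visits. The match is loose. With 30-day months, V3 is day 45–75 and dose 2 is day 22–28, so V3 falls 17–53 days after dose 2. V6 is day 225–255 and V5 is day 207–213, so V6 falls 12–48 days after dose 3.

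**The case against.** **The plan does not ignore baseline altogether.** A reader might infer that the trial has no baseline laboratory data, or that a vaccine effect could not be seen at all. Neither is supported. Screening values are collected and compared between groups, each group's median is described at every visit, and graded adverse events may catch individual abnormalities. A rise in both groups could be noticed across these tables. That stands, but it is an informal view with no test or interval for change. It also sets different people side by side: the baseline table is in the Full Analysis Set, which drops anyone without all three doses, while the safety medians are in the Safety Set.

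**The general principles name other tests.** Section 3.10.2 mentions a Wilcoxon rank-sum test for intragroup differences and a paired t-test for differences between groups. Neither is tied to laboratory values. The rank-sum test also ignores pairing: for no change in the elderly it rejected 0.6–1.0% at r = 0.5 and 0–0.1% at r = 0.7. Naming these tests does not cure the defect.

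**The SAP may cover it.** That is a fair answer on intervals for adverse-event rates, adjustment for sex or site, and tables of grade shifts, so these are not part of this point. It does not answer the laboratory analysis, where the protocol itself fixes the method for a primary endpoint.

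**The age contrast is intended, and the endpoint is largely descriptive.** Section 2.3 does name a younger control group, and no formal hypothesis is stated. An age comparison is legitimate, but it needs the baseline values to be interpretable.

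**Change from baseline is not a clean vaccine effect either.** This stands in full. Without an unvaccinated comparator, change cannot be separated from time, season or regression to the mean.

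**Conclusion.** The point holds for the planned laboratory tests and their intergroup intervals. They do not use the baseline values collected, cannot detect a change common to both age groups, and will flag age differences that preceded vaccination. The insensitivity to a common shift follows from the design and needs no assumption.

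The rate of false signals does rest on assumptions: about 36% per visit at an age difference of 0.2 SD, 67% at 0.3 and 98% at 0.5, against about 5% on change. A reader might infer a false alarm at nearly every visit. That needs the upper end of this range, and the protocol gives no figure to place the trial on it. A reader might also infer that a non-significant comparison of adverse events would be claimed as equal safety, but the protocol makes no equivalence or non-inferiority claim.

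Severity: should-fix. Laboratory values are one part of a largely descriptive safety endpoint, and the data needed for the better analysis are already scheduled.

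**What to change.** In section 3.10.2 (Primary analysis), for the Safety Set:

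1. Make the primary laboratory analysis the within-participant change from the screening value, by age group, with a Wilcoxon signed-rank test and 95% CI, at V2, V3 and V6. Name these as the visits that serve the one-month endpoint, and report the actual interval since the last dose. Change from screening at V3 reflects doses 1 and 2 together.
2. For dose 3, also report change from V5 to V6, provided it is confirmed that the V5 sample is drawn before the injection. The schedule does not say so.
3. Make any elderly-versus-young comparison on change, or adjusted for the baseline value.
4. Treat laboratory values at the other visits as descriptive.
5. State that, without an unvaccinated comparator, change describes the period after vaccination and is not by itself proof of a vaccine effect.

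The cost is wording and some programming, with no new data collection. The downside is that participants without a baseline sample drop out of the change analysis, so their number should be reported by group.

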## 3.12. Auditing

1. All research centers participating in clinical trials should adopt standard operating procedures to ensure the implementation of quality control and quality assurance systems for clinical trials;
2. To ensure the quality of the multi-center trial, before starting the formal trial, the principal investigators of each study site shall jointly discuss and formulate the protocol, and the relevant investigators shall be trained at the same time;
3. Each study site shall implement the trial according to a unified protocol;
4. Each study site will implement the same procedure to manage the trial vaccines, and the experimental vaccine manager must carefully store vaccines in accordance with the storage conditions proposed by the unit leader.
5. All observed results and abnormal findings in the clinical trials should be carefully verified and recorded in a timely manner to ensure the reliability of the data. All kinds of instruments, equipment, reagents, and standards used in the clinical trials must meet strict quality standards and function correctly under normal conditions. The recording and transfer of clinical data must be carried out by experienced investigators and supervised or verified to ensure data accuracy and scientific integrity. Clinical trial conclusions must be derived from the raw data.
6. The investigators in charge of the study should fill in the research medical records and CRF on time, completely, in detail, and accurately and submit or store documents according to the prescribed procedures after being signed and confirmed by a superior; all data related to the study must be centrally managed and analyzed.
7. To ensure the reliability and completeness of the trial data, the principal investigators of each study site, clinical research partners, and supervisors will monitor their clinical systems regularly to judge whether the implementation of the trial is consistent with the protocol and whether the reported data are consistent with the records of the study sites. A report will follow every visit.

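### The primary laboratory measures are analysed only as continuous variables, with no count of participants whose values become abnormal and no rule on whether such a value is an adverse event

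*Protocol*

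**What the plan says.** Section 3.4.1 defines the primary endpoint as "Safety profiles within one month after each vaccination dose, including" five items: AE incidence, liver function, kidney function, blood glucose and blood lipids. The four laboratory items carry no reference limit, grade or change criterion. On AEs, the section says "The definition and grade of AEs were evaluated according to the Common Terminology Criteria for Adverse Events, version 5.0", followed by general wording for grades 1 to 3.

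The Primary analysis paragraph of section 3.10.2 treats the two kinds of measure differently. AEs and SAEs are categorical: "The AEs/SAEs of the different categories will be summarized in percentages", compared by chi-square or Fisher's exact test. For the laboratory panels, "The laboratory test indices at each follow-up point will be statistically described as continuous variables". The two groups are then compared on ranks: "the Mann–Whitney U test will be used for intergroup comparisons". It adds: "The median values of the laboratory test indices for the two groups will be calculated at each follow-up point", together with intergroup differences and 95% CIs.

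Two other places bear on the point. The Principles of statistical analysis paragraph shows non-normal data as the median with the range. Section 3.12 requires that "All observed results and abnormal findings in the clinical trials should be carefully verified and recorded in a timely manner", but no analysis of those abnormal findings follows.

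**The concern.** Harm to the liver, kidney or glucose control after a vaccine could take the form of large rises in a few people rather than a small shift in everyone. The documents do not say which pattern to expect, so the plan should be able to show either. Medians and rank tests are chosen for their resistance to a few extreme values, so on their own they suit the first pattern poorly.

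The choice of comparison adds to this. Both groups receive the same vaccines (sections 3.3.1 and 3.3.2), so a difference in medians at a visit contrasts two age groups. Whether a value changed after a dose is a within-person question, and the Primary analysis contains no within-person laboratory summary.

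At stake is a primary laboratory result that reads as reassuring while a few elderly participants have clinically relevant rises, with no stated place in the report where they are counted.

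**Working it through.** The protocol gives no effect size, variance or power for the laboratory measures, so it has no figure of its own to reproduce. The check asks how far a few extreme values move the planned statistics.

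**Inputs from the protocol.** 200 elderly and 100 young (section 3.6); two-sided test at 0.05 (Principles of statistical analysis).

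**Assumed inputs.** Both groups log-normal with median 20 and log-SD 0.4 (0.2 and 0.6 also tried); k elderly values raised 6-fold or 10-fold; no other difference between the groups.

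**1. Mann–Whitney test.** Moving one elderly value from a typical rank to the top adds on average 100 × 0.5 = 50 to U. The standard error of U under no difference is √(200 × 100 × 301 / 12) = 708.3. The shift in z is therefore 50k / 708.3, and rejection is approximately Φ(shift − 1.96) + Φ(−shift − 1.96).

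| k of 200 | Shift in z | Rejection |
|---|---|---|
| 0 | 0 | 5.0% |
| 4 | 0.28 | 5.9% |
| 5 | 0.35 | 6.4% |
| 6 | 0.42 | 7.1% |
| 10 | 0.71 | 10.9% |
| 40 | 2.82 | 80.6% |

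This result does not depend on the assumed distribution or on the size of the rise, once the affected values are among the largest. Simulation agrees. With 6-fold rises in 4, 6 or 10 elderly, rejection is 5.6%, 6.8% or 9.6%, against 4.9% with none. With 10-fold rises in 5 elderly, it is 5.5% to 6.6% across the three log-SDs, against 4.0% to 4.9% with none, and the significance decision changes in about 4% of runs.

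**2. Median.** With k values moved to the top, the sample median sits at quantile 0.5 / (1 − k/200) of the unaffected values.
- k = 4: quantile 0.510, normal deviate 0.0256, median 20 × exp(0.4 × 0.0256) = 20.2.
- k = 6: quantile 0.515, normal deviate 0.0388, median 20.3.
- k = 10: quantile 0.526, normal deviate 0.0660, median 20.5.

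The shifts are 0.2, 0.3 and 0.5 on a base of 20, or about 1%, 1.5% and 2.5%. Simulation with 5 tenfold rises gives median shifts of 0.13 to 0.40 across the three log-SDs, while the mean moves by 4.6 to 5.4.

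**3. What a count would give.** Suppose every affected person, and nobody else, is classed as newly abnormal.
- 4/200 = 2.0% (exact 95% CI 0.6% to 5.0%); Fisher v 0/100, p = 0.31.
- 5/200 = 2.5% (0.8% to 5.7%); p = 0.17.
- 6/200 = 3.0% (1.1% to 6.4%); p = 0.18.
- 8/200 gives p = 0.056 and 9/200 gives p = 0.032.

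The count makes the cases visible and puts an upper limit on their rate. It does not make a handful of cases significant.

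**4. Why the pre-dose value matters.** With log-SD 0.4, a bare limit of 40 is exceeded by about 8.3 of 200 with no harm at all, since P(Z > ln 2 / 0.4) = 0.042. With 4, 6 or 10 affected it is exceeded by about 12, 14 or 18. A limit of 120 catches only half of those with a 6-fold rise: 2, 3 or 5. A count against one fixed limit therefore mixes background with new cases or misses cases. Comparison with the participant's own pre-dose value, on a stated grade or limit, addresses this.

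**The case against.** The strongest objection is that the trial is not blind to such cases. A reader might infer from the Primary analysis that severe individual elevations leave no trace in the primary result. The documents do not support that. First, the median-with-range rule would display the largest value at each visit. Second, grade 1 in section 3.4.1 covers asymptomatic cases and diagnostic observations, so an abnormal result without symptoms can be recorded as an AE and counted. The revision history also speaks of adverse reactions associated with coagulation or blood count, which suggests that the investigators link blood tests to adverse reactions.

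Both points stand, with limits. A range shows one maximum, not the number of people behind it or whether the value was already high before the dose. No sentence says when a laboratory value becomes an AE, so capture depends on each investigator's judgement.

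A second objection is that shift tables and listings belong in a statistical analysis plan. In general they do. Here, however, the protocol fixes the scale, test and summary for these primary measures, and uses proportions elsewhere: for AEs in the same paragraph, and for antibody positivity alongside titres in the Secondary analysis. Section 3.9 also places discussion of the statistical plan after database lock, so a criterion left until then might not be pre-specified.

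Third, a count of a few cases is no more significant than the rank test. That is correct and is conceded in the working. The distributions, the size of the rises and their frequency are likewise assumptions.

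**Conclusion.** The concern holds in a limited form. The planned laboratory analysis describes the centre of each group adequately but gives no individual-level account of abnormality, and the link between laboratory values and AEs is unstated. With 4 to 6 extreme values among 200 elderly, the rank test rejects in about 6–7% of trials against 5%, and the median moves by about 1–1.5% under the assumed log-normal with log-SD 0.4. About 40 of 200 would need extreme values for about 80% power.

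The rank result rests only on the group sizes and on the affected values being among the largest. The size of the median shift rests on the assumed distribution. It would go too far to say that the planned results would be literally unchanged, that the overall primary safety assessment would miss these cases, or that adding counts would make a few of them statistically significant. The change is worth making because it shows and estimates individual harm that the planned summaries can obscure.

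**What to change.** In the Primary analysis of section 3.10.2, add for each dose and age group:
- the number and percentage, with exact 95% CI, of participants whose post-dose value is newly abnormal or worse than their own pre-dose value, by a laboratory grade or reference limit stated in advance;
- a table of pre-dose category against worst post-dose category;
- a listing of all severe values.

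Keep the medians, differences and rank test as support. In section 3.4.1 or 3.11, state whether an abnormal laboratory value counts as an AE and by what criterion. That decision is for the investigators; the point is that it be written down and applied alike at both sites.

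The schedule in section 3.5 already has these tests at screening and at V2 to V9. V2 and V5 are also vaccination visits, so the text should say whether blood is drawn before the dose. V2 would serve both as the value after dose 1 and as the value before dose 2, so a second comparison with screening would keep a persisting rise from being classed as not new.

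The cost is protocol wording and one extra set of tables. No new samples are needed.
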